### **Data to be collected**

**Medical Record Data:** **Clinical Characteristics**, including cancer diagnosis, date of diagnosis, number of cancer survivor clinical encounters, hormonal laboratory assessments, prior hormone treatment, gonadotoxic therapeutic exposures [alkylating and heavy metal chemotherapy, gonadotoxic radiation], surgeries, history of hematopoietic cell transplant, and date of cancer treatment completion will be abstracted from participant's medical records by the site CRC using an adapted version of the COG Summary of Cancer Treatment Template.

[figure not shown]

**Quantitative Survey Data:** Participants will be invited to complete a web-based REDCap survey assessing sociodemographic and developmental factors, reproductive factors (knowledge, concerns, behaviors, and health needs), psychological factors, and history of FSA. The survey instrument is included with this protocol.

**Sociodemographic factors** include gender identity, race/ethnicity, religion, education level, household income, insurance and relationship status, and items are consistent with national surveys of young adults. **Developmental factors** will be assessed through the lens of emerging adulthood using The Markers of Adulthood (MoA) scale, which characterizes the attainment of behavioral milestones among emerging adults, and the IDEA-8 characterizes a self-perceived state of transition (e.g., feeling in-between); both scales have been used in large multi-site studies with emerging adults across diverse populations.

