**Fertility Status Assessment** will be assessed with the item "*Have you ever met with a reproductive specialist to assess your fertility? (e.g. reproductive endocrinologist or a fertility specialist)*". Participants who respond 'Yes' will also be asked details about this assessment (e.g., testing, results, discussion of infertility treatment options). Participants who respond 'No' or 'I don't know' will be asked their level of interest (Likert scale 1 [not at all interested] to 5 [very interested]), and perceived barriers to not receiving an FSA (e.g., lack of awareness, cost).

**Qualitative Interview Data:** Participants for the qualitative interviews will be identified through analysis of the quantitative survey if they (1) indicated on the survey that they are willing to take part in a qualitative interview and (2) responded to the survey item assessing receipt of an FSA. The interviewers for this study are English-speaking, therefore only participants who speak English will be invited to take part in the qualitative interview. We will use a qualitative descriptive approach, which is low-inference and seeks to describe the experiences of participants through their words and

experiences. In line with this approach, we will use maximum variation sampling, which is a preferred method for descriptive qualitative inquiry, to increase the representativeness of the sample in relation to the population being studied by recruiting participants across sites and those who have and have not received an FSA.

Interviews will be conducted until data saturation is reached; we estimate the sample size to be 32 participants, (8 at each participating site). We will try to have approximately equal number of participants who have and have not received FSA at each site, however, some sites may have higher success rates testing patients, therefore stratification of patients by FSA status may not be possible at the site level. However, we will ensure overall there are approximately 16 participants who have received an FSA and 16 who have not received an FSA.

The interview guide will be developed and informed by descriptive results from the quantitative survey. Planned interview questions include a discussion of factors that influenced participants' decision to pursue or not pursue FSA, satisfaction with that decision, barriers encountered when accessing FSA, and resources needed to support survivors who are interested in FSA.

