## **13. Local Number of Participants**

The study will recruit 325 participants study-wide, with 100 participants enrolled locally at the Children's Healthcare of Atlanta/Emory University site. Participant eligibility will be confirmed prior to recruitment.

The purpose of this study is to explore reproductive health and decisional factors regarding fertility status assessment. The sense of urgency and factors that influence the decision to pursue a fertility status assessment are different for females and males,

therefore our planned enrollment includes 100% female participants. Transgender men will also be eligible for this study; gender identity will be self-reported as part of the survey data collection.

Participants of any race and ethnicity will be recruited for this study. Estimates of race and ethnicity enrollments are derived from site-specific databases that were used to estimate demographics of survivors who would meet the eligibility criteria for this study. The race and ethnicity of survivors vary across sites and are related to the demographic characteristics of the geographical region. Overall, across all sites, we anticipate 76.9% of participants will be white, 12.6% Black, 6.4% more than one race, 2.2% Asian, 1.2% American Indian/Alaska Native, 0.6% Native Hawaiian or other Pacific Islander. We estimate that 13.1% of white participants will be Hispanic and 2.4% of Black participants will be Hispanic. These estimates align with previously published population-based studies of survivors of childhood cancer. The study survey will be available in Spanish for completion on REDCap or via paper and pen.

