#### **14. Recruitment Methods**

Recruitment procedures are based on strategies that have been successful with our research team in the past. The PI and research coordinator at each site will use site-specific databases, cancer registry data, or similar methods to identify patients who meet eligibility criteria (i.e., female sex, aged 18 through 29 years, history of cancer diagnosis <21 years of age, > 1 year from completion of cancer treatment, history of gonadotoxic treatment exposures). This approach has already been established and utilized at each site in order to provide details on estimated eligible participants. Once the list of potentially eligible patients is finalized, the list will be stratified by age group (18.00-24.99 and 25.00-29.99). Then each site will randomize their list, using excel or similar software, to begin consecutive recruitment. This approach will contribute to a more representative study sample. Site study teams will examine the medical records for patients prior to recruitment to verify eligibility.

The site research coordinator will recruit patients using various methods, depending on institutional approvals which include:

**Email/Epic MyChart.** An email/MyChart invitation including a link to the REDCap survey is the primary and preferred method of recruitment. The email will explain the purpose of the study, briefly outline the study procedures, and include site-specific contact information; there will also be instructions for patients to indicate if they decline participation and do not wish to be contacted further. Patients who are interested will click on the survey link. Participants will complete the REDCap survey (estimated time 15-20 minutes) and following completion the participant will be asked to provide contact information to receive the study gift card. A reminder email(s)/My Chart message can be sent for patients who do not respond.

**Phone Call:** For patients who do not complete the survey after receiving reminder emails/My Chart message, patients for whom email addresses are not available, and

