**Aim 1.3:** To assess associations between model parameters describing sociodemographic, clinical, reproductive health needs and decisional conflict (covariates) and receipt of an FSA (outcome), we will employ bivariable and multivariable binary logistic regression models. For all logistic regression models, model parameters for sociodemographic, clinical, reproductive health needs and decisional conflict will be treated as fixed effects and study sites will be evaluated as random effects, where appropriate, to account for potential differences in outcome variability between the study locations (i.e., clustering); moreover, fit statistics will be gauged (i.e., AIC, BIC, log-likelihood) for all regressions and appropriate assumptions will be checked, such as linearity in covariates and normality of residuals. Final multivariable results will be guided by the bivariable associations and determined using backward selection procedures, as well as any relevant clinician input. Estimates from these models will be presented as odds ratios for receipt of an FSA with 95% confidence intervals and p-values.

**Power Analysis:** The primary endpoint for this study will be receipt of an FSA. Based on insights from the literature, and our own clinical experiences, we anticipate 20% (n=65) of the sample will have received an FSA and 260 respondents will have not. These sample sizes, which will be obtained by sampling 4 study sites, achieve 80% statistical power to detect an odds ratio of 2.4 for discrete exposures. This odds ratio corresponds to 70.4% of respondents in the FSA group having the exposure, versus 50% of respondents in the non-FSA group having the exposure (i.e., a percent difference of 20.4%). Power was calculated in PASS v.14.0.8 (Kaysville, UT), with a two-sided un-pooled Z-test, an intra-cluster correlation (ICC) of 0.01, and a statistical significance level of 0.05.

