### 24. Resources Available

Recruitment will be stratified across age groups, with emphasis on the early years of emerging adulthood to ensure a developmentally-diverse sample; we will recruit two-thirds of the sample from participants 18.00-24.99 years of age (n=215) and one-third from participants 25.00-29.99 years of age (n=110). The estimated number of eligible patients by participating site is presented in **Table 1**. The pool of potential participants at each site is quite large, with an estimated 1758 female cancer survivors that meet eligibility criteria across sites. These estimates were obtained using site-specific clinical databases and cancer registry data. The enrollment target of 325 is just under 20% of those estimated to be eligible.

Table 1. Anticipated recruitment by participating site and age

| Participating Site | Estimated eligible by age stratification |              | Total estimated eligible | Planned recruitment |
|--------------------|------------------------------------------|--------------|--------------------------|---------------------|
|                    | 18.00-24.99y                             | 25.00-29.99y |                          |                     |
| Emory              | 376                                      | 105          | 481                      | 100                 |
| U of Cincinnati    | 297                                      | 148          | 445                      | 100                 |
| U of Colorado      | 355                                      | 177          | 532                      | 75                  |
| WashU/STL          | 201                                      | 99           | 300                      | 50                  |
| Total       | 1229                              | 529   | 1758              | 325          |

This study will recruit survivors from Emory University/Children's Healthcare of Atlanta, and three collaborating institutions, the University of Cincinnati/Cincinnati Children's, University of Colorado/Children's Hospital Colorado, and Washington University/St. Louis Children's Hospital. At each site, the site PI will oversee all aspects of the study, including maintaining regulatory and Institutional Review Board records, the identification and recruitment of eligible participants, and oversight of the site research coordinator. Sites will identify eligible patients using institutional databases or cancer

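### Aim 1.3 odds ratios are not protected against confounding by age and site: age is not a named model term, nothing is exempt from backward selection, and site is an optional four-level random effect

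*Protocol*

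**What the plan says.** **Outcome.** Section 19 defines the Aim 1 primary outcome as a yes to a survey item asking whether the respondent has ever met a reproductive specialist about her fertility. It is a lifetime measure.

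**Sampling.** Section 14: "the list will be stratified by age group (18.00-24.99 and 25.00-29.99). Then each site will randomize their list". Section 24: "Recruitment will be stratified across age groups, with emphasis on the early years of emerging adulthood", with targets of 215 younger and 110 older women. Table 1 plans 100, 100, 75 and 50 participants at the four sites.

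**Model terms.** Aim 1.3 names sociodemographic, clinical, reproductive health needs and decisional conflict parameters as fixed effects. Under Data to be collected, the sociodemographic factors "include gender identity, race/ethnicity, religion, education level, household income, insurance and relationship status". Age is neither in that list nor among the clinical characteristics abstracted from records.

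**Site.** For all logistic models, "study sites will be evaluated as random effects, where appropriate, to account for potential differences in outcome variability".

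**Selection.** Final models follow the bivariable associations, backward selection and clinician input. No term is held in.

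**What the protocol says about age and site.** Section 12 states that age and development influence decisional factors for fertility assessment. On site, the interview plan notes that "some sites may have higher success rates testing patients", and section 13 says "The race and ethnicity of survivors vary across sites".

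**The concern.** A woman of 29 has had longer to obtain an FSA than one of 18. The Background cites survivors without an FSA who were waiting until older (17%) or until in a relationship (20%). It also describes education, employment and relationship status as milestones that differ among emerging adults. Education, relationship status and the adulthood scales are candidate factors in this survey and plausibly move with age. Race/ethnicity is also a candidate and, by the protocol's own account, differs by site.

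In a model without age or site, such factors can carry age or site differences and be reported as related to FSA. Aim 1.3 is meant to supply targets for a decisional support intervention, so a factor that only tracks age or clinic would point it the wrong way.

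**Working it through.** **1. The plan's own power figure.** Inputs from section 19: 65 and 260 respondents, 70.4% against 50%, ICC 0.01, two-sided 0.05, un-pooled Z-test. With four clusters per group (m = 16.25 and 65), the design effects 1 + (m − 1) × 0.01 are 1.1525 and 1.64.

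SE = √(0.704 × 0.296 × 1.1525/65 + 0.5 × 0.5 × 1.64/260) = √(0.003695 + 0.001577) = 0.0726

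Power = Φ(0.204/0.0726 − 1.96) = Φ(0.85) = 80.2%, and the odds ratio is 2.38. The stated 80% and 2.4 are reproduced and are not in dispute.

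**2. Do the age quotas distort the sample?** Planned younger share: 215/325 = 66.2%. Eligible pool (Table 1): 1229/1758 = 69.9%. The two are close, so the quotas themselves do not create the problem.

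**3. Age left out of the model.** Assumptions, since the protocol gives no FSA rate by age: FSA rates that give about 20% overall, and a factor with no effect within age group, held by 20% of younger and 50% of older women.

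*FSA 13%/33.7%*, expected counts:
- FSA with factor: 215 × 0.13 × 0.2 + 110 × 0.337 × 0.5 = 24.1
- FSA without: 215 × 0.13 × 0.8 + 110 × 0.337 × 0.5 = 40.9
- No FSA with factor: 215 × 0.87 × 0.2 + 110 × 0.663 × 0.5 = 73.9
- No FSA without: 215 × 0.87 × 0.8 + 110 × 0.663 × 0.5 = 186.1
- Crude OR = (24.125 × 186.105)/(40.895 × 73.875) = 1.49; true value 1.00

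*FSA 16%/28%*: the same steps give (22.28 × 184.08)/(42.92 × 75.72) = 1.26.

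Simulated studies of 215/110 gave:

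| FSA younger/older | OR, no age term | False positives, no age | Age forced in | Age offered to backward selection | Age p<0.05 in full model |
|---|---|---|---|---|---|
| 13%/33.7% | 1.48–1.49 | about 28% | 5.6–5.8% | 5.9% | 98% |
| 16%/28% | 1.24–1.25 | 12–13% | 4.4% | 5.7% | 66% |

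Over a wider assumed range (FSA 18%/24% to 10%/40%; factor 40%/60% to 30%/80%), the crude null OR runs from 1.07 to 2.32.

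**4. Will the random site effect adjust for site?** I took the protocol's ICC of 0.01 on the logit scale, which is an assumption: between-site variance = (0.01/0.99) × π²/3 = 0.033. With sites of 100, 100, 75 and 50 and 20% FSA, the share of simulated studies with a variance estimate of zero was:

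| ICC | Moment estimator | Maximum likelihood |
|---|---|---|
| 0.01 | 47% | about 60% |
| 0.03 | 29% | about 37–41% |
| 0.05 | 20% | about 29% |

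A zero estimate leaves the model with no site adjustment.

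**5. Size of site bias.** Assumed FSA by site 15/18/22/30%, and a null factor held by 10/15/25/35%. Simulated OR: 1.18 with no site term, 1.09 with random site, 0.99 with fixed site. Rejection rates: 9.8%, 9.5% and 6.3%. These sites differ more than an ICC of 0.01 implies: their logits (−1.73, −1.52, −1.27, −0.85) have SD 0.38, against √0.033 = 0.18. The zero shares at ICC 0.01 therefore do not carry over to this example.

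**The case against.** The strongest reply is that age may well be intended. The sociodemographic list is introduced as what those factors include, so it need not be complete. The Non-participant data paragraph counts age with demographics and clinical characteristics, clinician input is kept in model building, and a full covariate list could sit in an analysis plan not shown here. This stands: the text does not exclude age. It does set a selection rule with no protected terms, and that is the point.

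Second, backward selection does most of the work if age is offered. Where age confounds strongly it is nearly always significant, and false positives stay near 6%. This stands for two-covariate simulations, and it limits the concern to the bivariable models and any model without age.

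Third, site is not ignored. A random effect is to be evaluated in all logistic models, and the power calculation carries an ICC. Random against fixed site is a modest difference (OR 1.09 against 0.99), and a zero variance estimate does not prove that material site confounding remains. This also stands.

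Fourth, crude t-tests and chi-square tests before an adjusted model are normal in an exploratory survey. Replacing them would be a preference.

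A reader might infer that the FSA outcome is in fact confounded by age and site, or that the stratified quotas cause this. The documents support neither. They give no FSA rate by age or site and say only that sites may differ, and the planned age mix is close to the eligible pool.

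**Conclusion.** The point holds as a lack of protection, not as demonstrated bias. For a lifetime outcome, the plan neither names age nor guarantees that it stays in the model, and its site adjustment is conditional and would often vanish at the protocol's own ICC.

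Without age, under the assumed gradients in the table, a null factor shows an OR of about 1.24 to 1.49 with 12% to 28% false positives. A reader might take the 28% as the error rate of the planned final model. It is not: it applies to models without age, and the figure is about 6% when age is offered to selection. Site bias in the assumed example is modest. All bias figures depend on assumed FSA and factor rates. The zero-variance figures depend on applying the ICC of 0.01 to FSA on the logit scale.

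This is a low-cost improvement worth making, and it does not invalidate the design.

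**What to change.** In section 19, Aim 1.3:

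- Name age (continuous) and site (four-level fixed effect, 3 degrees of freedom) as terms in every multivariable FSA model, exempt from backward selection.
- Delete the conditional qualifier on site.
- Report age- and site-adjusted odds ratios beside the crude bivariable ones, so that the results guiding selection can be read with that adjustment in view.
- Allow years since treatment completion as a candidate covariate.

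The t-tests and chi-square tests under Aims 1.1 and 1.2 may stay as descriptive comparisons.

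Cost: wording only. Age group and site are known from recruitment, and the treatment completion date is already abstracted. The forced terms use 1 + 3 = 4 degrees of freedom against about 65 FSA events, with slightly wider intervals.

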### **19. Data Analysis, Management and Confidentiality**

**Aim 1. Data Analysis:** Statistical analysis will be performed using SAS v.9.4 (Cary, NC) and CRAN R v.3.6 (Vienna, Austria), and statistical significance will be evaluated at the 0.05 threshold. Initial analyses will be undertaken to inspect data for errors, inconsistencies, and incomplete information. Data anomalies and outliers will be examined and corrected or removed if necessary. Descriptive statistics for sociodemographic and developmental factors, and clinical characteristics will be presented as means and standard deviations or medians and interquartile ranges for continuous variables and frequencies/percentages for categorical variables.

The primary outcome of Aim 1 is receipt of an FSA, defined as an answer of 'yes' to the survey item *"Have you ever met with a reproductive specialist to assess your fertility?"*. Based on prior research, and clinical experiences at the participating sites, we anticipate 20% of the sample will report receipt of an FSA.

**Aim 1.1. and Aim 1.2:** Descriptive statistics for reproductive health knowledge, values, health behaviors, and prevalence of reproductive health needs, as well as decisional conflict and fertility-related psychological distress, will be examined using means and standard deviations, medians and interquartile ranges, or percentages and frequencies, as appropriate. For the primary outcome variable (i.e., “yes” for an FSA), frequency and percentage will be calculated with a 95% confidence interval. Hypothesis tests between FSA cohorts (i.e., yes versus no) will be made using two-sample t-tests and chi-square tests of independence (or non-parametric equivalents such as Wilcoxon rank-sum and Fisher’s exact tests); moreover, effect sizes will be calculated to determine standardized differences in exposure values between the FSA cohorts and interpreted using Cohen’s *d* criteria: small (0.2), moderate (0.5), and large (0.8).

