**A2.2** The quantitative results and qualitative findings will be combined to generate meta-inferences regarding factors that contribute to FSA and barriers to be addressed through a decisional support intervention. This will include identifying critical content and resources to include in the decisional support intervention and refining measurement tools and outcomes for the testing of the intervention.

**Aim 3. Data Analysis:** To assess associations between model parameters describing sociodemographic, developmental, clinical, psychological, and reproductive health factors (covariates) and decisional satisfaction regarding FSA (outcome), we will employ bivariable and multivariable general linear regression models. Decisional satisfaction scores range from 0-100, with lower scores representing a good decision. Similar to methods for Aim 1.3, model parameters for sociodemographic, clinical, reproductive health needs and decisional conflict will be treated as fixed effects and study sites will be evaluated as random effects, as appropriate. Estimates from the regression models will be presented as slopes and least-squares means with 95% confidence intervals, p-values and effect sizes. Data transformations, including natural logarithms or inverse hyperbolic sine, may be applied to meet model assumptions, and if normality cannot be achieved, non-parametric methods or alternative modeling strategies (such as generalized additive models or regression splines) will be employed. Final multivariable

results will be guided by the bivariable associations and determined using backward selection procedures and any relevant clinician input.

Qualitative data will be integrated with the descriptive data and multivariable model results to further describe decisional satisfaction and associated concepts. This will help to examine decisional satisfaction as a relevant and modifiable intervention outcome and identify factors to be targeted through an intervention.

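### The final Aim 1.3 and Aim 3 models are picked by bivariable results and backward selection on about 65 events or observations, then reported with ordinary confidence intervals and p-values that ignore the selection

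*Protocol*

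**What the plan says.** For Aim 1.3 (Section 19), receipt of an FSA is modelled by bivariable and multivariable logistic regression. The final multivariable results are "guided by the bivariable associations and determined using backward selection procedures", and relevant clinician input may also be used. Estimates are "presented as odds ratios for receipt of an FSA with 95% confidence intervals and p-values". The assumption checks for these logistic models include "linearity in covariates and normality of residuals".

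For Aim 3 (Section 19), decisional satisfaction is modelled by general linear regression with the same rule: the final results are "guided by the bivariable associations and determined using backward selection procedures and any relevant clinician input". Estimates are slopes and least-squares means, with confidence intervals, p-values and effect sizes. Section 6 limits decisional satisfaction to participants who have received an FSA.

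For both aims "statistical significance will be evaluated at the 0.05 threshold". On the number of events, Section 19 says "we anticipate 20% (n=65) of the sample will have received an FSA and 260 respondents will have not". The protocol states no pre-specified covariate set, limit on model size, shrinkage, internal validation or multiplicity control for these models.

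**The concern.** A confidence interval or p-value computed as if the model had been fixed in advance is not valid when the same data chose the model. Terms stay because their estimates happened to be large. Noise terms enter with p<0.05 attached, real effects that survive are overstated, and intervals are too narrow and off-centre. The fewer the events per candidate, the worse this gets.

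This is a method that the protocol states, not a detail left open. An analysis plan could add thresholds, but it would have to depart from the protocol to remove the problem. Section 2 says Aim 3 identifies factors to be targeted by a future decisional support intervention, and Aim 1 is meant to inform that intervention. A false factor could therefore become a target.

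A separate, smaller error is that normal residuals are not an assumption of binary logistic regression. At any fitted probability the raw residual can take only two values, so a normality check there tells the analyst nothing useful.

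**Working it through.** **1. The plan's own figure.** The protocol says the sample sizes "achieve 80% statistical power to detect an odds ratio of 2.4 for discrete exposures", meaning "70.4% of respondents in the FSA group having the exposure, versus 50% of respondents in the non-FSA group". Inputs from Section 19: 65 and 260 respondents, 4 sites, ICC 0.01, two-sided unpooled Z-test, alpha 0.05.

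- Odds ratio: (0.704/0.296)/(0.5/0.5) = 2.38, about 2.4.
- Design effects 1+(m−1)×0.01, with m = 65/4 = 16.25 and 260/4 = 65: 1.1525 and 1.64.
- Standard error: √(0.704×0.296×1.1525/65 + 0.25×1.64/260) = √(0.003695+0.001577) = 0.0726.
- Power: Φ(0.204/0.0726 − 1.96) = Φ(0.85) = 80.2%.

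The stated 80% reproduces. It covers one exposure tested alone, so it says nothing about a selected multivariable model.

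**2. Candidate count (assumption).** Counted from Section 6, before dummy coding:

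- Narrow, following the covariate list in Aim 1.3: 7 sociodemographic + age + about 11 clinical + 2 reproductive health needs (leaving out interest in an FSA, which is asked only of those who did not answer yes) + 4 decisional conflict subscales = 25.
- Wide, with all listed factors: 7 + 1 + 11 + 2 developmental scales + 4 knowledge and perceived-risk measures + 3 reproductive concerns subscales + 4 distress scores + 3 behaviours + 3 needs + 4 decisional conflict subscales = 42.

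Events per candidate: 65/25 = 2.6, falling to 65/42 = 1.5.

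**3. Simple formula.** If no candidate has an effect and tests are independent, the chance of at least one false factor is 1 − 0.95^k:

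| k | Chance |
|---|---|
| 4 | 18.5% |
| 6 | 26.5% |
| 25 | 72.3% |
| 30 | 78.5% |
| 40 | 87.1% |
| 42 | 88.4% |

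**4. Simulation of the procedure.** Assumptions: half the candidates binary and half continuous; a bivariable screen (none, p<0.20 or p<0.05), then backward elimination at 0.05; correlation 0 or 0.3; no site effect and no clinician input. Aim 1.3 uses n=325 with about 65 events; Aim 3 uses n=65. There were 1000 runs per setting, with 30-40 candidates.

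| Setting | At least one false factor |
|---|---|
| Aim 1.3, no true effects, no screen or p<0.20 | 79-88% |
| Aim 1.3, no true effects, p<0.05 screen | 69-86% |
| Aim 1.3, five true effects, no screen | 79-90% |
| Aim 1.3, five true effects, p<0.20 screen | 62-77% |
| Aim 3, no true effects, no screen or p<0.20 | 79-92% |
| Aim 3, no true effects, p<0.05 screen | 68-87% |
| Aim 3, five true slopes of 0.5 SD | 70-94% |

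A separate simulation with 25-40 candidates, and either a p<0.20 screen or none, gave 67-84% for Aim 1.3 and 75-83% for Aim 3.

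**5. Inflation.** In Aim 1.3 with three true odds ratios of 1.35 per SD and 30 candidates, the retained ones averaged about 1.52. With five true effects, a true odds ratio of 1.5 appeared as a median of about 2.2-2.3, 2.0 as 2.5-2.6, and 2.4 as 2.8-3.0. In Aim 3, retained true slopes of 0.5 SD averaged about 0.8 SD.

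**6. Coverage.** Nominal 95% intervals of retained terms covered the truth about 50-57% of the time with three true effects in Aim 1.3. With five true effects the range was 34-74% in Aim 1.3 and 27-55% in Aim 3. These figures include retained false terms, whose intervals exclude the null almost by construction because they were kept for p<0.05.

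**The case against.** The strongest reply has four parts.

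- **The study is exploratory.** Its factors are to be combined with interview findings before intervention content is set, so the regression is not the only product. This stands and softens the consequence. It does not make the intervals correct.
- **Selection is not purely mechanical.** Clinician input is part of the rule and the simulations leave it out. It could help if it fixes terms in advance. It is unspecified, however, and if it is applied after results are seen it adds further freedom.
- **Key inputs are assumed.** The protocol gives no candidate count, screening threshold or stay level. The 0.05 is its general significance threshold, and it also mentions AIC and BIC. This stands, which is why ranges are shown. Even at 25 candidates the formula gives 72.3%.
- **One-at-a-time estimates are already planned.** This is true, but the protocol states no multiplicity control for them, and the final results come from the selected model.

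A reader might go further and use about 42 events, from the 13% FSA rate in the preliminary data (0.13×325). The documents do not support treating that as the expected figure. It is documented receipt in one clinic's records at mean age 19.2, whereas this study uses self-report, draws one-third of its sample from ages 25 to 29, and cites sources for 20%.

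**Conclusion.** The point holds. For both aims the protocol fixes a selection procedure on about 65 events or observations and attaches inference that ignores it. At least one false factor is likely: roughly 60-90% of studies in Aim 1.3 and 70-90% in Aim 3, depending on screen, correlation and true effects. Retained estimates are inflated on average, and intervals of retained terms cover far less than 95%. The sizes rest on an assumed 25-42 candidates, an assumed 0.05 stay level, and no modelling of clinician input or site.

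A reader might infer that false factors are near certain. The simulated range does not support that; likely is the right word. Nor does inflation of odds ratios extend to Aim 3, which reports slopes and least-squares means. The residual-normality check is a minor wording error for the logistic models only; it is a proper check for the linear models of Aim 3.

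**What to change.** - Before analysing associations with FSA receipt or decisional satisfaction, pre-specify from the conceptual model in Section 5 a small main model for each aim, sized to about 65 events or observations. Handle site as the protocol plans and fit the model without data-driven selection. State the clinician input at this stage. For comparison, 4 to 6 fixed terms carry an 18.5-26.5% chance of any false factor when no effect is real.
- Report the remaining factors as one-at-a-time estimates with false-discovery-rate control, labelled exploratory.
- If selection is kept, fix the candidate list and selection rule in advance, report bootstrap inclusion frequencies and optimism-corrected (shrunken) estimates, and do not present naive p-values and intervals as confirmatory.
- For the logistic models, replace the residual-normality check with checks of linearity in the logit, separation, influence and calibration.

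The cost is revised wording and a little more analysis; no new data are needed. The downside is that fewer factors can be called significant.
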